### Exclusion criteria:

- A clinical diagnosis of HNPCC (non hereditary polyposis colorectal cancer) or FAP (familial polyposis coli),
- Local resection for colorectal cancer (e.g., TEM-procedure),
- Life-expectancy less than 2 years due to concurrent disease (e.g., cardiac disease, terminal multiple sclerosis, liver cirrhosis),
- Inability to provide informed consent or refusal to do so,
- Inability to comply with the control or intense follow-up programme,
- Participation in other clinical trials interfering with the control-programmes
- Other or previous malignancies (except for non-melanoma skin cancer)

Informed consent (written) is obtained within 30 days after the primary tumour classification has been obtained. Patients refusing to participate should be asked for consent to be followed in the cohort, using data on their actual control-programme and their clinical course.

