### **Randomisation and treatments**

Randomisation will take place by Internet from a central randomisation unit (appendix 12) placed at Department of Clinical Epidemiology in Århus Denmark. Randomisation will be stratified according to tumour stage and clinical centre. Randomisation will be blocked in variable groups of which the size will be kept secret for the participating centres. The allocation procedure should be concealed to the deliverers of treatment.

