### **Study Follow-up Regimens**

CEA will (if possible) be measured on all colorectal cancer patients before surgery or preoperative adjuvant therapy, and one month after the completion of primary treatment. All patients should have “clean colon” within 3 months perioperatively, and at least one imaging procedure (Ultrasound, MRI, or CT) of the liver and X-ray of the lungs perioperatively. In both groups, an unlimited number of endoscopies are allowed. Interval diagnostic evaluation will be allowed for all subjects presenting symptoms.

A clinical visit 4-6 weeks after operation is recommended for information and allocation.

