| Adjuvant chemotherapy planned:                                                                             |                                                                                                                                                                                                                                                                                                                                                                                                                              |
| Colonoscopy for clean colon or X-ray of Barium performed preoperatively or planned 3 months after surgery: |                                                                                                                                                                                                                                                                                                                                                                                                                              |
| Signed consent for participation:                                                                          |                                                                                                                                                                                                                                                                                                                                                                                                                              |
| Date of filling in the form:                                                                               |  (dd-mm-yy)                                                                                                                                                                                                                                                                                                                                                                                                                            |

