#### *Exclusion criteria*

- Clinical diagnosis of HNPCC or FAP
- Local resection for colorectal cancer (e.g., TEM procedure)
- Life expectancy less than 2 years due to concurrent disease (e.g., cardiac disease, terminal multiple sclerosis, liver cirrhosis)
- Inability to provide informed consent or refusal to do so.
- Inability to comply with the control or intense follow-up programme.
- Participation in other clinical trials interfering with the follow-up programmes

*Informed consent* (written) will be obtained within 30 days after surgery and after the primary tumor classification has been made. Patients refusing to participate will be asked for consent to be followed in an observational analysis, using data on their actual follow-up program and their clinical

course.

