### **6) *Analysis of follow-up data***

Trial participants will be followed from the date of radical surgery for colorectal cancer until the date of the analyzed study outcome, date of dropout, date when lost to follow-up, or at 10-year follow-up, whichever comes first.

The Kaplan-Meier method and the log-rank test for between-group comparisons will be used to analyze 10-year overall mortality in the post-trial group participants. The colorectal cancer-specific mortality rates will be calculated using a cumulative incidence function and treating death associated with other causes as competing events. Risk differences in the 10-year overall and colorectal cancer-specific mortality will be calculated with corresponding 95% confidence intervals.

The main analyses will be stratified by cancer stage and will be repeated for the subgroups of patients diagnosed with rectal and colon cancer.

In the first sensitivity analysis, we will repeat the main analyses for trial participants from Denmark and Sweden. The overall and colorectal cancer-specific mortality rates will be compared between the 2 countries.

In a second sensitivity analysis, Cox proportional hazards regression will be used to compute crude and adjusted hazard ratios for overall and colorectal cancer-specific mortality rates. The hazard ratios will be adjusted for age at the time of colorectal cancer surgery; sex; colorectal cancer type; cancer stage; comorbidities including diabetes, cardiovascular disease, pulmonary disease, and cerebrovascular disease; preoperative radiation; adjuvant chemotherapy; and smoking.

The level of significance will be  $P < .05$  with a 2-sided test. Statistical software package SAS (SAS Institute, Inc., Cary, NC, USA) will be used for data management and analyses.

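### The 10-year SAP leaves out clinical centre, one of the two randomisation strata; the log-rank test may be mildly conservative as a result, and two smaller wording gaps should be closed.

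*Combined protocol and SAP*

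**What the plan says.** **Strata.** The protocol, under Randomisation and treatments, states: "Randomisation will be stratified according to tumour stage and clinical centre". The 5-year SAP names the same two factors under the same heading. Section 6 of the 10-year SAP stratifies its main analyses by cancer stage and repeats them in colon and rectal subgroups. Denmark and Sweden are examined in a first sensitivity analysis. A second sensitivity analysis fits Cox models and reports crude and adjusted hazard ratios. The adjustment list covers age, sex, cancer type, stage and comorbidities and closes with "preoperative radiation; adjuvant chemotherapy; and smoking". Centre is in none of these analyses.

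**Time origin.** The same section says: "Trial participants will be followed from the date of radical surgery for colorectal cancer". It specifies no delayed entry. The protocol, under Study Follow-up Regimens, says: "A clinical visit 4-6 weeks after operation is recommended for information and allocation". Consent timing differs a little between documents. In the protocol it "is obtained within 30 days after the primary tumour classification has been obtained"; in the 5-year SAP it "will be obtained within 30 days after surgery and after the primary tumor classification has been made".

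**Chemotherapy covariate.** The 10-year SAP does not define it. The protocol's pre-randomisation datasheet has a field labelled "Adjuvant chemotherapy planned".

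**The concern.** When allocation is blocked within centre, the design removes most of the chance imbalance between arms that is due to centre. A test that ignores centre still counts that variation in its variance, so its p-values are somewhat too large when centres differ in mortality. Leaving a prognostic factor out of a survival model also pulls the estimated effect slightly towards the null, which costs power. The introduction to the 10-year SAP says the trial was not entirely conclusive and showed a small difference of possible clinical importance. Precision that costs nothing is worth having in that setting.

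The time origin matters for a different reason. The named endpoints are absolute 10-year mortality rates. A patient who dies before allocation cannot enter the trial, so each participant is credited with a few weeks in which death could not be observed.

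The chemotherapy covariate matters because a value recorded at baseline is safe to adjust for. Treatment received after an open allocation might not be.

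**Working it through.** The 10-year SAP states no sample size, event count or power, so it has no figure of its own to reproduce. The protocol supplies the planning values: 5-year mortality 60%, difference 6 points, 2,500 patients.

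**1. Effect of omitting centre (simulation)**

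Inputs from the documents: N = 2,500; 24 centres (section 1 of the 10-year SAP, including Uruguay, which the 10-year analysis excludes); 60% mortality at 5 years. For 60% against 54%, the hazard ratio is ln(0.46)/ln(0.40) = 0.8475. Blocks of 4 are one of the two sizes in the 5-year SAP.

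Assumptions: constant hazard; normal centre effects on the log hazard with SD 0, 0.2 or 0.4; 10 years' follow-up from randomisation; two-sided 5% test; 2,000 simulated trials per setting. Stage was not modelled, so the comparison is an unstratified log-rank test against one stratified by centre.

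| Centre SD | Type I error, no centre | Type I error, with centre | Power, no centre | Power, with centre |
|---|---|---|---|---|
| 0 | 5.45% | 5.75% | 96.45% | 96.25% |
| 0.2 | 4.6% | 4.7% | 95.1% | 95.65% |
| 0.4 | 3.4% | 5.0% | 93.3% | 95.65% |

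Simulation error is about 0.5 points for type I error and 0.4-0.6 points for power. Only the SD 0.4 row shows a clear difference, and it is in the conservative direction.

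**2. Effect of the surgery clock on absolute mortality**

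Let h = -ln(1 - m)/5, where m is 5-year mortality. If 10 years are counted from surgery and allocation comes g years later, only 10 - g years at risk are counted. Mortality at the horizon then falls by exp(-10h) × [exp(hg) - 1]. The gap g is 28/365.25 = 0.0767 for 4 weeks and 42/365.25 = 0.1150 for 6 weeks. The value m = 60% is the protocol's; 30% and 15% are assumed in order to show a range.

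| m | h | 10-year mortality from randomisation | Fall, 4 weeks | Fall, 6 weeks |
|---|---|---|---|---|
| 60% | 0.1833 | 84.0% | 0.23 points | 0.34 points |
| 30% | 0.0713 | 51.0% | 0.27 points | 0.40 points |
| 15% | 0.0325 | 27.8% | 0.18 points | 0.27 points |

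For example, m = 30% at 6 weeks: 0.49 × [exp(0.0713 × 0.1150) - 1] = 0.49 × 0.0082 = 0.0040.

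**3. Effect of the surgery clock on the comparison**

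For 60% against 54% at 5 years, the 10-year risk difference from randomisation is 0.46² - 0.40² = 0.2116 - 0.1600 = 5.16 points. From surgery it is 5.19 points with a 4-week gap and 5.20 with a 6-week gap. In the simulation, the gap was drawn uniformly from 0 to 3 months. With no centre effect, type I error was 5.35% on the surgery clock and 5.45% on the randomisation clock, and power was 96.5% and 96.45%. Across all settings the two z statistics correlated at 0.997-0.998.

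**4. The chemotherapy covariate**

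No arithmetic applies. The other adjustment variables (age, sex, comorbidities, smoking, preoperative radiation, tumour site, stage) can all be derived from the pre-randomisation datasheet. The only adjuvant chemotherapy field on the reproduced forms is the planned one, on that same sheet; the follow-up form shows none for receipt. The protocol's Data collection section does promise detail on initial adjuvant treatment and on cancer treatment after randomisation, so a received variable could exist.

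**The case against.** The strongest reply is that the randomised comparison is intact. Section 3 of the 10-year SAP analyses patients as allocated, and section 2 keeps an intention-to-treat analysis. Both surveillance schedules are timed from surgery, so surgery is a coherent time scale. The gap to allocation has the same expected length in both arms. Country is examined, and the documents give no figure for variation between centres. All of this stands, and it limits the point to precision and wording.

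A reader might go further and infer that the 10-year analysis as a whole has come loose from randomisation. The documents do not support that: arms are compared as randomised, and the clock barely moves the difference or the test.

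A reader might also infer that the Cox model adjusts for treatment begun after allocation. That is not established. The SAP does not say planned or received, and the baseline field is a natural reading. The protocol's inclusion and exclusion chart also requires the same indications for adjuvant therapy in both groups. Any effect would be confined to one adjusted hazard ratio in a second sensitivity analysis, reported beside its crude counterpart; the main analyses do not adjust for chemotherapy.

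The reply does not answer the omission of centre. Country is coarser than centre, was not a randomisation stratum, and enters only as a sensitivity analysis.

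**Conclusion.** The omission of centre is a real but minor departure from analysing the trial as it was randomised. At an assumed centre SD of 0.4 it costs about 2.4 points of power (95.65% - 93.3%) and makes the test conservative; at 0.2 or 0 the change is within simulation error. It would be wrong to read it as inflating type I error, since no run showed that. These figures rest on the planned 2,500 patients and on all 24 centres, whereas the 10-year analysis drops Uruguay. They concern the log-rank test only; the Cox model was not simulated.

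The surgery origin is a smaller matter: 0.2-0.4 points on absolute 10-year mortality under a constant hazard and the recommended 4-6 week gap, with almost no effect on the arm difference. The documents give no actual times from surgery to randomisation.

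The chemotherapy covariate needs a definition and nothing more.

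**What to change.** In section 6 of the 10-year SAP:

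- Stratify the log-rank test and the Cox model by stage and clinical centre. Set in advance a rule for pooling small centres, or for using country where strata are sparse.
- Either take randomisation as time zero, or keep surgery as the time scale with delayed entry at randomisation.
- Define the adjuvant chemotherapy covariate as the planned field on the pre-randomisation datasheet.

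The first and third changes cost only wording: centre was needed for the stratified allocation, and the planned field is on the form. The second depends on the randomisation date being held. The server procedure in Appendix 10 implies that it is, but the reproduced forms show dates of operation and form completion and no randomisation date, so this should be confirmed first.
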